## Abstract

**Background:**

Although screening, brief intervention, and referral to treatment (SBIRT) is an evidence-based technique that, in some health-care settings, has been shown to cost-effectively reduce alcohol and drug use, research on the efficacy of SBIRT among criminal offender populations is limited. Such populations have a high prevalence of drug and alcohol use but limited access to intervention, and many are at risk for post-release relapse and recidivism. Thus, there exists a need for treatment options for drug-involved offenders of varying risk levels to reduce risky behaviors or enter treatment.

**Methods/design:**

This protocol describes an assessment of SBIRT feasibility and effectiveness in a criminal justice environment. Eight-hundred persons will be recruited from a large metropolitan jail, with the experimental group receiving an intervention depending on risk level and the control group receiving minimal intervention. The intervention will assess the risk level for drug and alcohol misuse by inmates, providing those at low or medium risk a brief intervention in the jail and referring those at high risk to community treatment following release. In addition, a brief treatment (eight-session) option will be available. Using data from a 12-month follow-up interview, the primary study outcomes are a reduction in drug and alcohol use, while secondary outcomes include participation in treatment, rearrest, quality of life, reduction in HIV risk behaviors, and costs of SBIRT.

**Expected value:**

Individual reductions in alcohol and drug use can have significant effects on public health and safety when observed over a large population at risk for substance-use problems. With wider dissemination statewide or nationwide, a relatively low-cost intervention such as SBIRT could offer demonstrated benefits in this population.

**Trial registration:**

Clinical Trials Government Identifier, NCT01683643.

## Introduction

Nearly all people with a history of drug use enter the criminal justice system at some time in their drug use career, frequently on a recurring basis. Drug use is closely associated with crime, and its prevalence among offenders is high [1-3]. Drug use, particularly when involving injection, also contributes to increased risk of HIV transmission [4]. Relapse to drug use tends to occur within the first few months of release from incarceration [5,6], highlighting the importance of providing intervention options at the pre-release or reentry phase of the offender’s incarceration.

While many offenders use drugs at levels that do not necessarily require treatment, they are still at risk of progressing to abuse or dependence or of engaging in unhealthy behavior. Interventions for offenders at low or moderate risk are largely lacking within the criminal justice system. One strategy to address this would be to provide early intervention to offenders using approaches that are appropriate to level of risk. Such an intervention would provide appropriate care earlier than would otherwise be the case, curtailing progression to higher risk levels and reducing risky behaviors. Offenders who are serving a jail sentence, particularly on drug charges, are at a “teachable moment” in which they may be amenable to an intervention designed to reduce their risk of relapse and re-arrest and improve other behaviors.

Screening, brief intervention, and referral to treatment (SBIRT) provides universal low-cost screening to a target population using brief, valid, and reliable screening instruments. Based on results from the screening, counselors, health educators, or other staff can identify people at different risk levels and provide types and intensities of intervention in accordance with the level of risk, ranging from information or brief intervention for low-risk users to referral to formal treatment for high-risk users [7]. Through a combination of prevention/early intervention and formal treatment, SBIRT is a public health approach intended to have a positive impact on the drug- and alcohol-related behavior of a broad user population, rather than on the much smaller population of those diagnosed with abuse or dependence. Studies in health-care settings have reported that the costs of SBIRT are relatively low, and that the benefit-cost ratio is favorable ($3-$4 for every dollar spent) [8].

Less research has been conducted on brief interventions or SBIRT for drugs than for alcohol. But many randomized studies of brief intervention for drug use have found statistically significant effects for at least one of the primary outcomes [9-15] an exception is [16]. Also, published articles on SBIRT projects for drug use funded by the US Substance Abuse and Mental Health Services Administration (SAMHSA) have reported significant reductions in drug use and other problems from baseline to follow-up [17-20], although use of a single-group design in these projects precludes strong conclusions about the causal effect of SBIRT on drug use. Also, limited research bearing on the use of brief intervention or SBIRT with offenders is available. Three randomized studies suggest that brief intervention can result in positive behavioral change among offenders [12,21,22].

In summary, although SBIRT has been found to be effective in some populations in health-care and other settings, it remains an empirical question whether SBIRT is a feasible intervention for offenders and whether it encourages treatment participation, reduces substance use, and results in other longer term benefits. Given the large proportion of offenders who use drugs and alcohol and who experience problems associated with such use, a relatively low-cost intervention such as SBIRT could have significant public health and public safety implications.

### Study aims

The aims of the SBIRT for Offenders study are to a) assess the effectiveness of SBIRT with jail inmates in terms of participation in a graduated series of interventions (brief intervention, brief treatment, and referral to longer term treatment), depending on risk level; b) determine the effectiveness of SBIRT with jail inmates on public health and public safety outcomes at 12 months following study admission, namely, drug use, alcohol use, criminal activity, arrest, reincarceration, HIV risk behaviors, and quality of life; and c) determine the cost of providing an SBIRT intervention to jail inmates. To accomplish these aims, we will recruit jail inmates who are completing their sentence in a large Los Angeles County jail. The study will be a collaboration between the University of California at Los Angeles (UCLA) Integrated Substance Abuse Programs (ISAP), the Los Angeles County Sheriff’s Department, Homeless Health Care Los Angeles (HHC-LA), and the Substance Abuse Prevention and Control Division of the Los Angeles County Department of Public Health.

## Methods/design

### Setting and participants

Screening and brief intervention will occur in two jails in Los Angeles County. Men’s Central Jail houses approximately 5000 male inmates from throughout Los Angeles County. The Twin Towers Detention Facility houses about 400 female inmates from throughout the county. The majority of inmates at both facilities have been sentenced on misdemeanor charges. As noted above, brief treatment will be conducted by trained counselors from HHC-LA, either in person at the HHC-LA treatment program or by telephone. Participants needing longer term treatment will be referred to one of the county’s Community Assessment Services Centers.

Since SBIRT is intended to be a universal intervention within a target setting, all adult (18+) male and female inmates who are within two weeks of scheduled release and who are available during the times that recruitment is conducted will be eligible to participate, with the following exceptions: those who 1) lack fluency in English or Spanish, 2) are unwilling to provide locator information for follow-up, 3) plan to leave the Los Angeles area within 12 months, 4) already have a referral to treatment following release from jail, or 5) are unable to provide informed consent owing to cognitive impairment.

### SBIRT for Offenders intervention

The conceptual framework of SBIRT is informed by empirical and theoretical considerations. There is a continuum of substance use problems and awareness of those problems among users. Screening, brief intervention, and referral to treatment systematically identifies, through screening, an individual’s level of risk and provides (or at least offers) an intervention that is appropriate to the assessed level of risk. The type and intensity of the intervention depend on the level of risk and the degree to which the individual is ready to make changes, as posited in the Stages of Change model (Pre-Contemplation, Contemplation, Preparation, Action, and Maintenance [23]). Most participants in the study will be in the Pre-Contemplation or Contemplation stage and, in any case, are not likely to be actively seeking treatment. For the brief intervention component of SBIRT, the therapeutic technique to help clients move to the Preparation or the Action stage is typically motivational interviewing, using the FRAMES model (Feedback, Responsibility, Advice to change, Menu of options, Empathy, and Self-efficacy [24]). The SBIRT model used in the study will include the components typical of SBIRT models generally: 1) screening to identify level of risk and, depending on the level of risk, 2) information, 3) brief intervention, and 4) referral to treatment.

### Screening and risk-level interventions

Screening is intended to identify individuals at varying levels of risk associated with the use of alcohol and/or drugs. It is not intended to provide a formal diagnosis (which is the function of clinical assessment), but rather to provide guidance for deciding which level of intervention may be needed to address the identified level of risk. As explained below, all participants in the study will complete the Alcohol, Smoking, and Substance Involvement Screening Test (ASSIST) [25] for screening. The ASSIST is an eight-item instrument developed by the World Health Organization (WHO) to screen for hazardous, harmful, and dependent use of alcohol, tobacco, and drugs. The ASSIST typically takes about 5-10 minutes to administer, although it can take longer depending on the number of drugs used over the lifetime. For each drug endorsed, questions are asked about frequency of use in the three months prior to the current incarceration, problems related to use, dependence indicators, and injection drug use. Following ASSIST administration, separate risk scores are calculated, with scores falling within a low-, moderate-, or high-risk range. Table 1 shows the risk-level scores for alcohol and drugs and the indicated intervention for each risk level, as specified in the WHO brief intervention manual [26]. We will use a computer-based version of the ASSIST to make the screening faster to administer and score.

**Table 1 T1:** ASSIST risk scores and level of intervention

	**ASSIST alcohol score**	**ASSIST drug score**	**Intervention**
Low risk	0-10	0-3	Feedback on ASSIST score, literature
Moderate risk	11-26	4-26	Feedback on ASSIST score, literature, brief intervention
High risk	27+	27+	Feedback on ASSIST score, literature, brief intervention, referral to treatment

#### Low risk for drug and/or alcohol use

Study participants in the SBIRT group who score at low risk on the ASSIST for drug or alcohol use are notified by the health educator of their screening score and its meaning and are given literature on drug and alcohol use, HIV risk behaviors, and HIV testing. The health educator provides clients with a list of treatment resources should their behavior change in the future or to share with affected family or friends.

#### Moderate risk for drug and/or alcohol use

For users of drugs and alcohol who score at moderate risk on the ASSIST, the health educator provides feedback on the screening score and provides a brief intervention to encourage cessation of use, a description of brief treatment and its benefits, and a referral to brief or other treatment if the client requests it. The health educator also provides participants at this risk level with literature on the effects of drug and alcohol use and on HIV risk behaviors and HIV testing. (Although the ASSIST assesses tobacco risk, because of time constraints the intervention will not address tobacco use; however, the literature provided will include advice on smoking cessation).

The brief intervention takes about 15-20 minutes and uses a motivational interviewing approach. The health educator reviews the screening score and its meaning, assesses readiness to change, establishes goals with the client, and reviews strategies for change. One of the strategies is the opportunity to participate in a brief treatment intervention upon release from jail. If requested by the client, the health educator provides a referral to more intensive treatment.

Brief treatment (BT) is an individual-based intervention that is intended for clients who score at moderate risk. It is designed mainly to help clients who have few complicating problems to learn and develop skills to change their behavior. It is also appropriate for those who score at high risk but who are unwilling to commit to longer term treatment or for those who are on a waiting list for longer term treatment. It is offered at no cost to participants assigned to the SBIRT condition. The study will use a BT model developed for a SAMHSA-funded SBIRT program in San Diego, which was also used in a previous Los Angeles SBIRT project; it has been modified as needed for use in the study. This manualized treatment utilizes elements of two evidence-based practices: motivational interviewing and cognitive behavioral therapy [24,27,28] and consists of eight highly structured sessions delivered in person or by telephone. The initial session consists of orientation to BT and a needs assessment using the Addiction Severity Index-Lite (ASI-Lite) [29]. In Sessions 2-7, the counselor builds on the findings of the initial assessment by monitoring the client’s progress toward meeting self-defined goals in the areas of substance use, relapse prevention, HIV risk behaviors, and other identified psychosocial needs. In Session 8, the counselor reviews with the client his or her progress toward meeting self-defined goals, provides positive verbal reinforcement, and discusses future steps towards goals. If the client requests more intensive treatment, the counselor provides a referral as described below.

#### High risk for drug and/or alcohol use

For clients who score at high risk, the health educator gives feedback on the screening score and conducts a brief intervention to encourage the client to accept and follow through on a referral to a specialty treatment program. Information on HIV risk behaviors and testing is also provided. The health educator refers clients to one of 19 Community Assessment Services Center (CASC) offices located throughout Los Angeles County; the CASCs conduct assessments for substance use disorders and other problems and then refer clients to appropriate treatment programs, most of which offer comprehensive services, including HIV/AIDS education and HIV testing and counseling. The health educator provides the client with the name, telephone number, and address of the CASC located near where he or she lives or works. The county Department of Public Health has multiple sources of funding for persons who wish to receive treatment but do not have health insurance. Should the client prefer BT, the health educator sends the person’s contact information to the counselor, who will arrange for an in-person or telephone appointment.

### Selection and training of SBIRT health educators and counselors

Homeless Health Care-Los Angeles (HHC-LA) will provide SBIRT to jail inmates assigned to the intervention group. The HHC-LA health educators (who provide screening and brief intervention) and counselors (who provide BT) will be individuals who have experience working with offenders with substance use problems. They will need to receive clearance to work in the jails. They will participate in a week-long training in study design, administration, and scoring of the ASSIST, brief intervention, BT, and procedures for referral to treatment. Training will be provided by the principal investigator (study purpose and design), the project director (ASSIST, brief intervention, referral), and a consultant on BT. Training in the components of the intervention will be conducted in a small-group format with use of presentations, demonstrations, role-playing, and videotaping of practice sessions to ensure that the health educators and counselors are familiar with the material, have mastered the techniques, and have received appropriate feedback. The BT consultant will provide refresher training every six months. In addition, a clinical supervisor at HHC-LA will hold weekly meetings with health educators and counselors. Staff will be bilingual in English and Spanish, and literature will be available in English and Spanish.

### Human subjects approval

The study procedures and the informed consent form have been approved by the UCLA General Campus Institutional Review Board.

### Power analysis for sample size

Average effect sizes from meta-analyses of brief interventions for alcohol problems [30-32] range from a standardized mean difference of 0.18 to 0.43. Although no meta-analyses have been conducted on brief interventions for drug problems, effect sizes from primary studies involving illicit drugs [9-11,14,33] range from 0.13 to 0.84. Most of these studies focus on clients in primary care or other health-care settings. No experimental studies have reported outcomes for SBIRT (as opposed to brief intervention) with offenders. Since previous research provides limited guidance for estimating the expected effect sizes for the primary outcomes of the study, it seems reasonable to assume a small effect size; that is, a standardized mean difference of about 0.20 for a reduction in alcohol and drug use from baseline to 12-month follow-up. The power analysis (using the RMASS2 program; [34]) assumes alpha = 0.05 (two-sided), power = 0.80, an attrition rate of 15%, and an autoregressive variance-covariance structure, with a moderate correlation of 0.50 between levels of use at baseline and follow-up. With an expected effect size of 0.20 for the primary outcomes, the sample size is 778, equally divided between the two study groups. This estimate is similar for different variance-covariance structures, including a random-effects structure. We set the total sample at 800. To assess possible treatment by gender interactions, the sample recruited will include 25% women.

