### Tracking and locating for 12-month follow-up interviews

At baseline, the interviewer will ask participants to fill out a Locator Form. This form contains information that is useful for locating participants for follow-up interviews (e.g., driver’s license; names, addresses, and phone numbers of immediate relatives and unrelated friends; areas of town frequented; locations where social services are received; and probation or parole officer contacts). Other tracking resources include local and state correctional agencies that maintain publicly available websites that can be searched to determine whether a subject is in jail or prison or is on probation or parole. We will use a program developed in FileMakerPro^®^ for previous ISAP studies to record information needed for the tracking and locating process (e.g., locator data, agency contacts, letters, telephone calls, appointments). Tracking and locating procedures are described in a manual that was developed at ISAP [42] and is widely distributed by NIDA and CSAT. These procedures have been used by ISAP researchers in many studies to track and locate subjects for as long as 10 years between interview points, with follow-up rates typically at 85% or more [43]. Follow-up interviews have been conducted with subjects who are homeless, who are in jail or prison, who have absconded from probation or parole supervision, or who reside in other states or countries. In short, we expect that the detailed locator information from participants and the successful strategies used in previous studies will enable us to locate 90% of the baseline sample and, allowing for refusals and deaths, to interview at least 85% of the sample at the 12-month follow-up. We will obtain criminal justice and treatment records covering the 12-month follow-up period on all participants.

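### The printed sample size of 778 is not reproduced from its stated inputs if variances are equal; 800 with 15% attrition then gives about 74–77% power, not 80%

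*Protocol article*

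**What the plan says.** The section on power analysis for sample size defines the target as "a standardized mean difference of about 0.20 for a reduction in alcohol and drug use from baseline to 12-month follow-up". It says that the calculation "assumes alpha = 0.05 (two-sided), power = 0.80, an attrition rate of 15%, and an autoregressive variance-covariance structure". The two waves are taken to correlate at 0.50. The result is: "With an expected effect size of 0.20 for the primary outcomes, the sample size is 778, equally divided between the two study groups". The total is then set at 800. No variances are given for either wave, and the text does not say which standard deviation standardises the 0.20.

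The section on tracking and locating repeats the attrition assumption from the other side: the investigators expect "to interview at least 85% of the sample at the 12-month follow-up". The Variables section says that the power analysis is based on the two primary outcomes. The section on hypothesis testing tests change over time by repeated-measures GEE.

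**The concern.** Attrition is listed among the inputs that produce the sample size, so a reader takes 778 as already allowing for 15% loss. With a correlation of 0.50 and equal variances, the textbook requirement for this effect is slightly above 778 before anyone is lost. A figure below the no-loss requirement cannot also contain a 15% allowance unless some other input differs from what is printed.

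The figure supports both primary outcomes. If the trial finds no effect, readers will take it to have had 80% power at 0.20 SD with attrition covered. If the printed inputs are the ones that apply, that is somewhat too favourable.

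**Working it through.** **Inputs from the power section:** effect d = 0.20 on change; correlation r = 0.50; two-sided alpha 0.05 (z = 1.960); power 0.80 (z = 0.842); attrition 15%, so q = 0.85 are followed up; equal allocation; 778 calculated, 800 planned.

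**Assumption not in the document:** equal variance at baseline and 12 months, set to 1. The variance of change is then 2(1 − 0.50) = 1, so the SD of change equals the SD of the level. It does not matter which of the two standardises the effect.

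**Formulas.** Total N = 4·v·(1.960 + 0.842)² / d², where v is the variance factor. Power = Φ(d / √(4v/N) − 1.960). The effect detectable with 80% power is 2.802·√(4v/N).

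**Attempt to reproduce 778.** With no attrition v = 1, so N = 4 × 7.849 / 0.04 = 784.9. At 778 with no loss, power is 79.7%. The printed figure is about 7 people (0.9%) below the no-loss requirement.

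**With 15% attrition, three ways of handling incomplete participants:**

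- Attrition-weighted two-wave contrast (all at baseline, 85% at follow-up): v = 1 + 1/0.85 − 2(0.50)/√0.85 = 1.092. This form is assumed to approximate the program that was used.
- Likelihood model that keeps baseline-only participants: v = 0.75/0.85 + 0.25 = 1.132.
- Completers only: v = 1/0.85 = 1.176.

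| Handling | v | N needed | Power at 778 | Power at 800 | Detectable at 800 |
|---|---|---|---|---|---|
| No attrition | 1.000 | 785 | 79.7% | 80.7% | – |
| Attrition-weighted | 1.092 | 857 | 76.1% | 77.2% | 0.207 SD |
| Likelihood | 1.132 | 889 | 74.6% | 75.7% | 0.211 SD |
| Completers | 1.176 | 924 | 73.0% | 74.1% | 0.215 SD |

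For exactly equal groups, 785, 857 and 889 become 786, 858 and 890. A 20,000-run simulation at 800 with 15% loss gave 75.6% for the likelihood model and 73.7% for completers.

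**The margin from 778 to 800** is 22 people. Fifteen percent of 800 is 120, which leaves 680, below 785.

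**Other ways to arrive at or near 778.** These show what cannot be ruled out:

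- Effect 0.21 with attrition-weighting: 784.9 × (0.20/0.21)² × 1.092 = 777.3. That is 388.6 per group, rounded up to 389, or 778 in total.
- Unequal variances, for illustration a follow-up variance 1.25 times baseline (an assumption). With attrition-weighting, the variance of the contrast is 1 + 1.25/0.85 − √1.25/√0.85 = 1.258. If 0.20 is in follow-up SDs, d² = 0.04 × 1.25 = 0.05 and N = 4 × 7.849 × 1.258 / 0.05 ≈ 790. If it is in baseline SDs, d² = 0.04 and N ≈ 987.

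**The case against.** The strongest reply is that the document does not give enough to say what went into the program. Variances are not stated, and the effect is first described as approximate. An effect of 0.21 with attrition included gives exactly 778, and one illustrative unequal-variance case gives about 790. This stands. A reader might infer from the closeness of 778 to 785 that attrition was simply omitted, but the document does not establish that. It shows only that the printed inputs and the printed result do not agree under equal variances. If rounding of the effect is the explanation, the discrepancy remains, because the result is stated for 0.20.

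A second reply is that baseline adjustment restores the power. At correlation 0.50 it needs 784.9 × 0.75/0.85 = 692.5, so 693, and 800 gives about 85%. That is true of such an analysis, but it does not reproduce 778, and the power section does not describe it. The hypothesis-testing section adjusts for covariates only if the groups differ significantly at baseline. The unadjusted comparison of proportions at follow-up does not help either: with an arcsine effect of 0.20 it has the same requirement, 785 complete or 924 with loss.

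Third, completers-only is the least favourable case, and the missing-data section plans maximum likelihood or multiple imputation. This is fair, and it is why the range is given. The most favourable of the three still needs 857.

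Finally, a reader might take the sentence "This estimate is similar for different variance-covariance structures, including a random-effects structure" to be an empty check, since with two waves, equal variances and one correlation several structures coincide. The document does not support going that far. A random-effects structure may include a random slope, which can give unequal variances at the two waves and so a different matrix.

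**Conclusion.** The point holds as a mismatch between printed inputs and printed result. Under equal variances at the two waves and an effect of exactly 0.20, 778 does not deliver 80% power with 15% attrition. The planned 800 gives about 74–77% for the change contrast, or 80% for about 0.207 to 0.215 SD. The shortfall is 3 to 6 percentage points. That is modest for an effect size that the authors themselves chose with limited guidance, but it affects how a null result would be read.

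The conclusion depends on the equal-variance assumption and applies to the change contrast that the section powers. The lower figure of 857 also depends on the assumed attrition-weighted formula. The cause of the mismatch is undetermined: omitted attrition, a rounded effect and unequal variances all remain possible.

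**What to change.** Keep the total at 800. Re-run the calculation and state the variance at each wave, which SD standardises the effect, the exact effect size and how attrition enters. Then do one of two things:

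- show the inputs that reproduce 778 with 15% attrition; or
- restate the power at 800 with 15% attrition as about 74–77% for 0.20, equivalently 80% for about 0.21 SD, on the change contrast.

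Power at other values of the baseline-to-follow-up correlation would be informative but is optional. The cost is one re-run and a few sentences. No participants are added and the design does not change. Under the second option the stated power becomes slightly less favourable.
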